## **B. Hypothesis and Aims to be Tested**

We hypothesize that additional therapy with a combination of TEAS and DCEAS produces better outcomes than routine care alone in improving depression and other psychiatric sequelae of domestic violence; the therapeutic effects of acupuncture may be associated with varying modulation of blood biomarkers. To test this hypothesis, an assessor-blinded, randomized controlled trial will be conducted to pursue the following the two aims: (1) to compare the effectiveness of routine care with and without additional TEAS and DCEAS in treating depression, and other psychiatric symptoms of domestic violence women victims; and (2) to determine baseline-to-endpoint changes in levels of blood biomarkers, and their correlations with clinical outcomes.

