## **C. Plan of Investigation**

**Outline:** This is an assessor-blinded, randomized controlled trial. A total of 110 women victims of domestic violence aged 18-65 years will be recruited from local community centers and domestic violence shelters (refugee centers). They will be randomly assigned to routine care combined with (n = 55) and without (n = 55) additional acupuncture (TEAS+DCEAS) for 12 weeks. The study flow chart are presented in Fig. 3. Acupuncture therapy will be conducted with 2 DCEAS sessions at clinics and 3 TEAS sessions at home each week. The primary outcome is the Beck Depression Inventory II (BDI-II) for depression. Secondary outcomes include the 17-item Hamilton Depression Rating Scale (HAMD-17) for depression, Perceived Stress Scale (PSS) for stress, PTSD Check List-Civilian Version (PCL-C) for PTSD symptoms, Insomnia Severity Index (ISI) for sleep and 12-Item Short Form Survey (SF-12) for quality of life. Two 10-ml blood samples will be drawn respectively at baseline and at the end of 12-week study for measurement of blood biomarkers, respectively. The SPIRIT diagram of all assessments at enrolment, allocation, and different time points can be found in Fig. 4.

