##### **(a) Data analysis**

One biostatistician who is blinded to interventions will be responsible for statistical analysis. Descriptive statistics tables will be used to present basic information on all variables. For continuous variables, the mean and standard deviation (or medians, 25th, and 75th percentiles) will be presented; while for categorical variables, the number of participants in each category and its percentage will be presented separately. The analysis will be carried out on the intention-to-treat (ITT) population. All eligible participants will be included in the analysis. Missing data on the primary outcome will be imputed using the multiple imputation method under the missing at random (MAR) assumption followed by sensitivity analysis.

The primary outcome will be analyzed by a linear mixed-effects model with repeated-measures, with adjustment for the baseline; visit, treatment, and the visit  $\times$  treatment interaction as the fixed effect, and individual subject as the random effect. A significant two-way interaction will be considered to demonstrate whether the treatment group has a greater change in the BDI-II score from baseline to assessing points than the routine care group. The effect of the treatment will be estimated by the difference between treatments, and will be presented together with its associated 95% confidence intervals (CIs). A similar approach will be applied to other continuous outcomes.

For the response rate and remission rate, logistic regression, with adjustment for baseline scores, and Chi-square ( $\chi^2$ ) test will be used. The definition of responder is subjects with  $\geq 50\%$  reduction from the baseline BDI-II score; the definition of remission is subjects with BDI-II score less than 10. Subjects who discontinue treatment prior to having a post-baseline BDI-II score will be considered non-responders/not remission.

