Subgroup analysis will be further conducted to detect whether demographic and baseline clinical variables are associated with outcomes. Student t-test and Wilcoxon rank sum test will be used to detect differences in continuous baseline variables and biomarker levels between the two groups. Categorical baseline variables, including discontinuation and incidence of adverse events will be analyzed using Chi-square ( $\chi^2$ ) test or Fisher's exact tests. Linear mixed-effects model will be conducted to examine intercorrelations between clinical outcomes and biomarker levels and among biomarker levels. Statistical significance is defined as a two-tailed  $P < 0.05$ .

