#### **D. Anticipated results and potential pitfalls**

Our previous studies have confirmed the effectiveness of TEAS and DCEAS in patients with depression, PTSD, and OCD.[9,10,14-17] We also have done a series of intervention, epidemiological, and methodological studies in domestic violence women victims. These provide a direct and solid basis to ensure the success of the proposed study. Additional acupuncture is expected to produce the superior efficacy than routine care alone in improving psychiatric symptoms occurred in stress trauma of domestic violence. Multiple correlations between outcomes and biomarkers would be identified.

Although local collaborative network, protocols, and research team have been well established, according to our previous studies, slow recruitment progress often happened due to unpredictable causes. If the recruitment could not reach the goal as scheduled timeline at the end of the first year, additional study sites and promotion plan will be sought.

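### The between-group biomarker test named in the analysis section specifies no time point, change or baseline adjustment, although Aim 2 concerns change and every biomarker is sampled at baseline and Week 12

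*Protocol*

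**What the plan says.** Section B (Hypothesis and Aims) gives the second of two aims as "to determine baseline-to-endpoint changes in levels of blood biomarkers, and their correlations with clinical outcomes". The Outline in section C provides the data: "Two 10-ml blood samples will be drawn respectively at baseline and at the end of 12-week study for measurement of blood biomarkers". The Fig. 4 schedule agrees, with blood sampling at Week 0 and Week 12 only.

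In section C(iv), Data analysis, biomarkers are named in two sentences. The first covers the comparison between arms: "Student t-test and Wilcoxon rank sum test will be used to detect differences in continuous baseline variables and biomarker levels between the two groups". The second covers the associations: "Linear mixed-effects model will be conducted to examine intercorrelations between clinical outcomes and biomarker levels and among biomarker levels".

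The same section handles the clinical scales differently: "The primary outcome will be analyzed by a linear mixed-effects model with repeated-measures, with adjustment for the baseline". It then adds a general extension: "A similar approach will be applied to other continuous outcomes". Biomarkers are not named in that extension. They are also not in the list of primary and secondary outcomes, either in the Outline or in section C(iii)(a), Clinical assessment.

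**The concern.** The aim is about change, and the design collects the paired samples needed to study it. The analysis sentence names two-sample tests on levels and puts biomarkers alongside baseline variables. Both natural readings fall short:

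- **Baseline levels.** The test compares two randomized groups before treatment and says nothing about change.
- **Week-12 levels.** The test addresses a treatment effect but leaves out each woman's own starting value, which the trial has already drawn blood to obtain.

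What is at stake on the second reading is precision, plus exposure to chance baseline imbalance in a trial of 110 women. The protocol cannot be said simply to have left the method to a later document, because it names the tests and they do not fit the aim as stated.

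**Working it through.** **Inputs from the protocol.** Section C(i)(c), sample size: 55 per group, difference 6.55 and SD 10.8 on the BDI-II, 80% power, 20% dropout. Section C(iv), Data analysis: two-tailed 0.05. Section C(ii)(a): 1:1 allocation.

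**Assumed.** The protocol gives no SD, effect size or baseline-endpoint correlation r for any biomarker. Effects are therefore expressed in SD units of the level, and r is varied over 0.3, 0.5 and 0.7. Equal variance at both times is assumed.

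**The plan's own figure first.** n per arm = 2 × (1.96 + 0.842)² × (10.8/6.55)² = 42.7, so 43, and 43/0.8 = 53.75, so 54. With the t-distribution, n = 43.66, so 44, and 44/0.8 = 55. The stated 55 per group reproduces and is not affected by this point. Completers per arm: 55 × 0.8 = 44.

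**Detectable difference at 80% power, 44 per arm (normal approximation).**

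- Unadjusted Week-12 level: (1.96 + 0.842) × √(2/44) = 2.802 × 0.2132 = 0.597 SD.
- ANCOVA on own baseline: 0.597 × √(1 − r²).
- Unadjusted change score: 0.597 × √(2(1 − r)).

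**Power at a true difference of 0.5 SD.** Φ(0.5/(0.2132 × s) − 1.96), where s = 1 for the unadjusted level and s = √(1 − r²) for ANCOVA. For the unadjusted level: 0.5/0.2132 = 2.345, less 1.96 = 0.385, so 65%.

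| r (assumed) | Detectable, Week-12 level | Detectable, change score | Detectable, ANCOVA | Power at 0.5 SD, Week-12 level | Power at 0.5 SD, ANCOVA |
|---|---|---|---|---|---|
| 0.3 | 0.60 | 0.71 | 0.57 | 65% | 69% |
| 0.5 | 0.60 | 0.60 | 0.52 | 65% | 77% |
| 0.7 | 0.60 | 0.46 | 0.43 | 65% | 91% |

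The variance of the unadjusted Week-12 comparison is 1/(1 − r²) times that of ANCOVA: 1.10, 1.33 and 1.96 times at the three correlations.

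**Chance imbalance.** Suppose the arms differ at baseline by k standard errors and there is no treatment effect. The unadjusted Week-12 statistic then has mean r × k and SD √(1 − r²). For k = 2, it exceeds ±1.96 with probability of about 8%, 13% and 22% at r = 0.3, 0.5 and 0.7. For k = 1 the figures are 5.0%, 4.8% and 3.9%, so the problem is confined to unlucky allocations. Averaged over all allocations, the error rate stays at its nominal 5%.

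**The case against.** **The sentence does not say raw, unadjusted or Week 12.** That is correct. Aim 2 itself speaks of changes in levels, so a t-test on change scores is a possible reading, and it would address the aim. But the sentence does not say so. As the table shows, an unadjusted change score is worse than the plain Week-12 level at r = 0.3, equal at 0.5, and behind ANCOVA throughout. The wording needs settling on any reading.

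**The extension to other continuous outcomes may already cover biomarkers.** They are continuous, and the model it extends adjusts for baseline. However, biomarkers are not among the listed outcomes and have their own sentence with a different method. If the extension does cover them, the two sentences conflict. This makes the point partly one of reconciliation, and that much of the objection stands.

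**The gain may be small.** At r = 0.3 it is: 0.60 to 0.57 SD, and 65% to 69% power.

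Three stronger readings are tempting, and the documents do not support them:

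- *The biomarker comparison is biased.* An unadjusted Week-12 comparison is unbiased under randomization. What it loses is precision.
- *The association model will produce spurious correlations.* Two variables that both shift over 12 weeks can look linked if visit and arm are left out of a model of level on level. The protocol lists no fixed effects for this model, so the omission cannot be assumed, and the drift of any biomarker would have to be invented.
- *Uncorrected multiple testing undermines Aim 2.* The protocol does not say which of the markers in its introduction will be assayed, so the number of tests is unknown. Error control for a mechanistic aim is a matter of preference and is commonly set in the SAP. The remark in section D that "Multiple correlations between outcomes and biomarkers would be identified" is an expectation, not an analysis rule.

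**Conclusion.** The point holds as a mismatch between Aim 2 and the between-group biomarker test that the protocol names. None of the plain readings delivers an efficient comparison of change: baseline levels miss the aim, and Week-12 levels leave the baseline sample unused.

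On the Week-12 reading, the cost is 0.60 SD detectable against 0.57 to 0.43 SD with ANCOVA, for r from 0.3 to 0.7. This rests on 44 women per arm having both samples, on equal variances, and on correlations that the protocol does not supply.

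The association sentence is the weaker half. It speaks of levels where the aim speaks of change, but a mixed model with suitable terms could still serve.

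The consequence is moderate. Aim 2 is one of only two aims, but biomarkers are neither the primary nor a listed secondary outcome, and the sample size was not built on them. The change is worth making because it costs almost nothing, not because the trial's main conclusion is at risk.

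**What to change.** In section C(iv), Data analysis:

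1. Remove biomarkers from the t-test/Wilcoxon sentence. State instead that each biomarker will be compared between arms at Week 12 by ANCOVA with its own baseline value as covariate, on the log scale if skewed. The baseline-adjusted mixed model already given for the primary outcome is an equivalent choice, since with a single post-baseline sample it reduces to ANCOVA.
2. Say explicitly whether the sentence on other continuous outcomes includes biomarkers, so that only one method applies to them.
3. For the correlation part of Aim 2, relate the baseline-to-Week-12 change in the biomarker to the change in the clinical score with arm in the model. Alternatively, keep the mixed model and state that it carries visit and arm terms. Change on change matches the aim more directly.

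The cost is a few lines of text and slightly more programming. No extra blood samples, visits or participants are needed, and the sample size of 110 is unaffected.

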#### **D. Anticipated results and potential pitfalls**

Our previous studies have confirmed the effectiveness of TEAS and DCEAS in patients with depression, PTSD, and OCD.[9,10,14-17] We also have done a series of intervention, epidemiological, and methodological studies in domestic violence women victims. These provide a direct and solid basis to ensure the success of the proposed study. Additional acupuncture is expected to produce the superior efficacy than routine care alone in improving psychiatric symptoms occurred in stress trauma of domestic violence. Multiple correlations between outcomes and biomarkers would be identified.

Although local collaborative network, protocols, and research team have been well established, according to our previous studies, slow recruitment progress often happened due to unpredictable causes. If the recruitment could not reach the goal as scheduled timeline at the end of the first year, additional study sites and promotion plan will be sought.

#### **E. Impact on People's Health and Health Services as well as Plan to Disseminate Research Findings to End Users**

Women victims of domestic violence are a socially vulnerable population who need more intervention options in addition to routine cares. If the proposed study could demonstrate that acupuncture with a combination of TEAS and DCEAS is effective in treating violence trauma-caused psychiatric sequelae, we will introduce TEAS and DCEAS to physicians, Chinese medicine practitioners, nurses, social workers, and other caregivers of local communities and domestic violence centers via holding training workshops. Through these training workshop, TEAS+DCEAS could serve as an additional intervention for domestic violence victims.

| INTERVENTIONS (TEAS+DCEAS): |              |            |                 |    |    |
| Treatment group             |              |            | ←————→          |    |    |
| Routine care group          |              |            |                 |    |    |
| ASSESSMENT:                 |              |            |                 |    |    |
| BDI-II                      | X            | X          | X               | X  | X  |
| AAS                         | X            | X          | X               | X  | X  |
| HAMD-17                     |              | X          | X               | X  | X  |
| PCL-C                       |              | X          | X               | X  | X  |
| PSS-10                      |              | X          | X               | X  | X  |
| ISI                         |              | X          | X               | X  | X  |
| SF-12                       |              | X          | X               | X  | X  |
| Adverse Events              |              | X          | X               | X  | X  |
| Blood Sampling              |              | X          |                 |    | X  |
